#### Inclusion criteria

Patients eligible for the trial must comply with all of the following:Men or women, aged 14–65 years;Patients with asthma history or typical clinical symptoms;The diagnosis of mild and moderate asthma according to the Chinese guideline for the prevention and management of bronchial asthma [25], with increases in the forced expiratory volume in 1 second (FEV_1_) of > 12 % and > 200 mL from baseline;Agree with all procedures in this trial by signing a written informed consent form.

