### Sample size

Sample size will be based on the primary outcome of the asthma control test (ACT). According to our pilot study, we anticipate that the improvement of the ACT will be 3.5 points in the verum acupuncture plus as-needed salbutamol aerosol and/or prednisone tablets group and 1.6 points in the sham acupuncture plus as-needed salbutamol aerosol and/or prednisone tablets group. Based on a 0.8 power to detect a significant difference (*α* = 0.05, 2-tailed), 86 patients are required for each group with a 1:1 allocation rate. To compensate for dropout patients, we plan to enroll 100 participants per group, with 200 participants in total.

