### Randomization

After the completion of the baseline evaluation, eligible participants will be randomly classified into two groups: the verum acupuncture plus as-needed salbutamol aerosol and/or prednisone tablets group, the sham acupuncture plus as-needed salbutamol aerosol and/or prednisone tablets group. A computer-generated, blocked random allocation sequence will be performed by Drug And Statistics software 3.2.1 [26]. The receptionist who is not involved with data collection will provide the random number and group assignment immediately by using opaque, sealed envelopes. This procedure guarantees that randomization concealment is adequate, and will not be influenced by the acupuncture doctor or participants.

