#### Methods of statistical analyses

The modified intent-to-treat (mITT) analysis set will be considered as the full analysis set. This will include all evaluable patients: ie, all randomized patients who receive at least one treatment and who have a score at randomization and at least one post-randomization ACT total score. The mITT analysis set will be used for efficacy analyses. Missing data will be replaced according to the principle of LOCF (the last observation carried forward). The per-protocol (PP) analysis set will include only those mITT patients who have no significant protocol deviations and who received the treatment to which they were randomized. Analysis of primary efficacy endpoint will be repeated on the PP analysis set to test for robustness of results. All the randomized patients who receive at least one treatment and for whom any post-baseline safety data are available will be included in the safety analysis set. The safety analysis set will be used to assess safety variables.

In general, all efficacy and safety variables will be summarized using descriptive statistics and graphs as appropriate. Continuous variables will be summarized by descriptive statistics (sample size (*n*), mean, standard deviation (SD), minimum, median and maximum). Categorical variables will be summarized in frequency tables (frequencies and percentages). The primary efficacy variable, the change from baseline in ACT total score to the end of treatment period will be analyzed using an analysis of covariance (ANCOVA). The ANCOVA analysis will include the baseline ACT total score as covariate, treatment as a fixed effect and center as a random effect. Secondary endpoints will be analyzed using a *t* test or Wilcoxon rank sum test as appropriate. All analyses will be performed using SAS software, version 9.3 (SAS Inc., Cary NC, USA). All statistical tests will be conducted at a 2-tailed significance level of 5 %.

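### The primary ANCOVA leaves out severity class and baseline FEV1, both known at entry, and so forgoes a small, nearly free gain in precision

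*Protocol article*

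**What the plan says.** All references are to the protocol article.

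- **Inclusion criteria.** Both severity classes are eligible: "The diagnosis of mild and moderate asthma according to the Chinese guideline". The same criterion requires an FEV1 increase of more than 12% and more than 200 mL, so severity class and an FEV1 value are known before randomization. FEV1 also appears among the secondary outcomes.
- **Methods of statistical analyses.** The primary variable is "the change from baseline in ACT total score to the end of treatment period". The model terms are listed outright: "The ANCOVA analysis will include the baseline ACT total score as covariate, treatment as a fixed effect and center as a random effect". Neither severity nor FEV1 is among them.
- **Randomization.** The sequence is described as computer-generated and blocked. No stratification factor is named.
- **Sample size.** The calculation rests on expected ACT improvements of 3.5 and 1.6 points, power 0.8 and two-sided alpha 0.05. It gives 86 per group, raised to 100. No SD is stated, and no allowance for covariate adjustment is mentioned.

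**The concern.** Adjusting for baseline ACT is sound and takes out the part of severity that the questionnaire captures. ACT is a single symptom score, however, and guideline severity class and lung function may carry further information about how a patient changes over six weeks. Patients must be able to stop inhaled corticosteroids and other controllers, and baseline is one week without treatment. Two patients with equal ACT after that week could plausibly diverge according to underlying severity. The article does not measure this, so it is a reasoned possibility and no more.

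If it is so, the confidence interval for the ACT difference is wider than it need be. The plan has 80% power with no stated reserve beyond dropout, so a gain from data already in hand is worth a line in the plan. Naming the covariates in advance also avoids a later argument about adjustment if the arms turn out to differ visibly in severity.

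**Working it through.** **Inputs from the article.** Difference 3.5 − 1.6 = 1.9 points; power 0.80; two-sided alpha 0.05; 86 per arm needed, 100 per arm enrolled.

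**Inputs assumed.** Share with moderate asthma p = 0.5. Difference D between moderate and mild patients in ACT change, at equal baseline ACT, of 1, 2 or 3 points. The article gives neither.

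**1. The plan's own figure.** Without an SD, 86 cannot be reproduced forwards. Solving n = 2(z₀.₉₇₅ + z₀.₈₀)² SD² / 1.9² for the SD gives

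SD = 1.9 / [(1.960 + 0.842) × √(2/86)] = 1.9 / (2.802 × 0.1525) ≈ 4.45.

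The t-test version gives 4.42. I use 4.4, for which t-test power at 86 per arm is 0.804.

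**2. Variance explained by severity.** R² = p(1 − p)D² / SD², with SD² = 19.36.

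- D = 1: 0.25 × 1 / 19.36 = 0.013
- D = 2: 0.25 × 4 / 19.36 = 0.052
- D = 3: 0.25 × 9 / 19.36 = 0.116

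**3. Power after adjustment.** The residual SD is 4.4 × √(1 − R²). The patient equivalent is 172 × [1/(1 − R²) − 1], where 172 = 2 × 86.

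| D (points) | R² | Residual SD | Power at 86 per arm | Equivalent patients, both arms |
|---|---|---|---|---|
| none | 0 | 4.40 | 0.804 | – |
| 1 | 0.013 | 4.37 | 0.809 | 2 |
| 2 | 0.052 | 4.28 | 0.824 | 9 |
| 3 | 0.116 | 4.14 | 0.850 | 23 |

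A 50% mix maximises p(1 − p), so these are upper figures for each D. With 30% moderate and D = 2, R² = 0.21 × 4 / 19.36 = 0.043 and power is 0.821 instead of 0.824.

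**4. The same gain on a correlation scale.** Let r be the partial correlation of severity with ACT change, and start from 0.800 at SD 4.45 (normal approximation). Power is then 0.804, 0.816, 0.836 and 0.864 for r = 0.1, 0.2, 0.3 and 0.4. The SE falls by 0.5%, 2.0%, 4.6% and 8.3%.

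**5. What chance imbalance can do.** With 100 per arm and p = 0.5, the arm difference in share moderate has SD √(2 × 0.25/100) = 0.071. A difference of at least 10 percentage points has probability about 16% (normal approximation). It would move the estimate by 0.10 × D, that is by 0.1, 0.2 or 0.3 points. At the 95% limit of 13.9 percentage points the shift is 0.14, 0.28 or 0.42 points. The SE is 4.4 × √(2/100) = 0.62 and the target difference is 1.9. This variation is already part of the SE.

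The gain from FEV1 is not quantified, since nothing in the article supports even a range.

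**The case against.** The strongest reply is that the model is valid and pre-specified as it stands. It already adjusts for the baseline value of the endpoint and for center, and another covariate is a matter of preference. Every figure for the gain rests on assumed inputs. The 85% case needs patients with the same baseline ACT to differ by 3 points according to severity, which is more than the 1.9-point treatment effect itself. The SD of 4.4 comes from a two-group formula, so 80% is not shown to be the power of the planned ANCOVA. All of this stands, and it limits the point to a modest recommendation.

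It does not remove the point. The article lists the model terms, so the covariate set is a stated choice and not a detail left to a fuller document. The two omitted variables are available before randomization.

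A reader might go further in three ways that the article does not support.

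- **That a severity imbalance biases the result.** Under randomization, what remains after adjusting for baseline ACT is random error, which the SE and the 5% test already reflect.
- **That precision built into the design is thrown away.** That would require allocation stratified by severity, or a sample size that counted on adjustment. Neither is stated.
- **That one sequence was shared across the 12 centers without regard to center.** The article says only "A computer-generated, blocked random allocation sequence will be performed by Drug And Statistics software". It is silent on strata, and a condensed article commonly leaves such detail to the full protocol. Altering the allocation procedure while recruitment is under way would also not be free.

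**Conclusion.** The point holds as a minor improvement in efficiency. The primary ANCOVA adjusts for baseline ACT and center only, so any further prognostic information in severity class and baseline FEV1 stays in the error term. For severity, the likely gain is about half a power point to two power points (0.804 to 0.809 or 0.824), worth roughly 2 to 9 patients. The 0.850 case, worth 23 patients, needs a severity effect larger than the treatment effect and is less plausible. These figures rest on a back-solved SD of about 4.4, an assumed 50% moderate share and an assumed severity difference of 1 to 3 points. If severity adds nothing beyond baseline ACT, the gain is nil and the loss negligible. The validity of the planned test is not in question.

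**What to change.** In the section on methods of statistical analyses, before unblinding, add severity class (mild or moderate) and baseline FEV1 as pre-specified fixed covariates in the primary ANCOVA, next to baseline ACT, treatment and center. State that both values are those recorded before randomization.

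The cost is one line in the plan and two degrees of freedom out of about 170 (2 × 86 − 2 in the simple two-group comparison). No new data are needed, and the sample size and allocation procedure stay as they are. Recruitment was still running when the article was written, so the change could be made without sight of results by arm.

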### Procedure

An independent receptionist will initially assess each potential participant according to the inclusion and exclusion criteria. After confirmation of asthma diagnosis, participants will enter a baseline period of 1 week without treatment, during which they will be trained to use a peak flow meter, record peak expiratory flow (PEF) and maintain an asthma diary.

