### Interventions

Acupuncture will be performed by senior attending doctors at 12 clinical centers. Asthmatic patients randomly allocated will receive verum/sham acupuncture once every other day with a total of 20 treatment sessions in 6 weeks and 3 months follow-up (see Fig. 1). Patients are required to complete case report form (CRF), asthma quality of life questionnaire (AQLQ) and record daily asthma symptom scores, acute asthma episodes and the use of as-needed salbutamol aerosol and/or prednisone tablets in the asthma diary from the completion of screening test to the end of the follow-up visits. Salbutamol aerosol (100 μg/puff) will be taken as needed for asthma attack. If the symptoms are still not controlled within a maximum safe dose, prednisone tablets will be suggested to take at a dose of 20 mg each day for 3–5 days. Patients should record use of salbutamol aerosol and/or prednisone tablets in the asthma diary.

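### Secondary endpoints are tested without adjustment for baseline values that are already collected, which loses precision at no gain

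*Protocol article*

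**What the plan says.** All references are to the protocol article; no separate SAP is shown.

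- **Secondary endpoints** (Methods of statistical analyses): "Secondary endpoints will be analyzed using a *t* test or Wilcoxon rank sum test as appropriate". No covariate and no center term is named, and the section does not say whether final values or changes from baseline are compared.
- **Primary endpoint** (same section): "The ANCOVA analysis will include the baseline ACT total score as covariate, treatment as a fixed effect and center as a random effect".
- **Baseline data** (Procedure): in a one-week baseline period participants learn to "record peak expiratory flow (PEF) and maintain an asthma diary". Under Interventions, the AQLQ, daily symptom scores, acute episodes and as-needed medication use are recorded "from the completion of screening test to the end of the follow-up visits".
- **Timing** (Randomization): "After the completion of the baseline evaluation, eligible participants will be randomly classified into two groups". The baseline values therefore precede allocation and are legitimate covariates.
- **Allocation method** (Randomization): "A computer-generated, blocked random allocation sequence will be performed". Blocking balances group sizes. It does not balance the baseline values of the secondary endpoints.
- **FEV1** (Inclusion criteria): FEV1 reversibility is an entry condition, so a pre-randomization FEV1 very likely exists.

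**The concern.** The article names a baseline-adjusted model for the primary endpoint and then fixes a simpler, unadjusted one for the whole secondary list. This is a stated choice, not a gap left for a fuller document.

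For an outcome correlated with its own baseline, part of the between-patient spread can be explained before treatment starts. A two-sample test leaves that spread in the error term, so the confidence interval is wider than it needs to be. A chance difference between groups at baseline also carries over into the estimated effect.

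AQLQ, lung function and rescue use are likely to carry much of the clinical interpretation alongside ACT. What is at stake is the precision of those results, not the primary conclusion.

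**Working it through.** **Inputs**

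- n = 86 evaluable per group, two-sided α = 0.05 and power 0.80 (Sample size; Methods of statistical analyses).
- Baseline/follow-up correlation ρ: not in the documents. Assumed 0.6, range 0.3 to 0.8.
- Equal SD at baseline and follow-up (assumed), scaled to 1.

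**The plan's own figure.** The 86 per group is for ACT, with an expected difference of 3.5 − 1.6 = 1.9 points. No SD is given, so 86 cannot be reproduced, only inverted. It implies an SD of about 4.45 (normal approximation) or 4.42 (noncentral t). Nothing below depends on this; 86 is used only as the group size.

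**Relative variance of the treatment effect**

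- t test on final values: 1
- t test on changes: 2(1 − ρ)
- ANCOVA: 1 − ρ²

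So ANCOVA/final = 1 − ρ², and ANCOVA/change = (1 − ρ²) / [2(1 − ρ)] = (1 + ρ)/2. Both ratios are below 1 for every ρ strictly between 0 and 1. The direction therefore does not depend on the assumed value; only the size does.

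**Power.** With 86 per group, a t test has 80% power at a standardized effect of about 0.43. Dividing that effect by the square root of the variance ratio gives the power of ANCOVA for the same true effect:

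| ρ | ANCOVA/final | power if t test on final values has 80% | ANCOVA/change | power if t test on changes has 80% |
|---|---|---|---|---|
| 0.3 | 0.91 | 84% | 0.65 | 94% |
| 0.6 | 0.64 | 94% | 0.80 | 88% |
| 0.8 | 0.36 | >99% | 0.90 | 84% |

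At ρ = 0.6 the unadjusted test would need 86/0.64 ≈ 134 patients per group (final values) or 86/0.80 ≈ 108 (changes) to match ANCOVA with 86.

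**Chance imbalance.** One standard error of the baseline difference is √(2/86) = 0.152 SD. Given such an imbalance, the final-value estimate shifts by ρ × 0.152 = +0.05 to +0.12 SD for ρ from 0.3 to 0.8. The change-score estimate shifts by −(1 − ρ) × 0.152 = −0.11 to −0.03 SD. The two shifts have opposite signs; under ANCOVA the shift is about zero.

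The gain from a center term is not quantified, because the documents give no between-center variance.

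**The case against.** The strongest reply is that the stated analysis is sound. Baseline precedes randomization, so the two-sample tests are unbiased on average and hold their 5% level. The primary endpoint, on which the trial is sized, is already adjusted. This stands, and it limits the point to efficiency and to bias conditional on an observed imbalance.

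It can also be said that baseline is not necessarily ignored, because a test on change scores uses it. This stands too. The article does not say which is meant, so the final-value figures are conditional. With change scores the gain at ρ = 0.6 is smaller and the imbalance is over-corrected rather than left uncorrected. ANCOVA remains the more precise in either case.

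The correlation is an assumption. For diary endpoints the baseline covers only one week and could be weakly predictive. This is why a range is shown.

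A reader might infer more than the text supports:

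- *More false positives.* No: the 5% level already allows for chance imbalance.
- *Every secondary interval is too wide.* No: EOS has no explicitly stated baseline measurement, and one baseline week tells little about exacerbation counts.
- *The choice between t test and Wilcoxon is made after seeing the data.* The article gives no criterion, but such a rule is commonly left to the SAP, which is not shown.
- *Monthly follow-up visits are treated as unrelated comparisons.* The article does not say how, or at which visits, the secondary endpoints are tested.
- *The secondary analyses contradict the primary one.* A simpler method for secondary endpoints is not a contradiction.

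**Conclusion.** The point holds as a free improvement, for secondary endpoints only. The planned tests are valid but less precise than an analysis that uses the baseline values already collected.

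It is clear for PEF, daily symptom scores, symptom-free days, rescue medication use and AQLQ, and very likely applies to FEV1. At ρ = 0.6 and 86 per group, 80% power would become about 94% or about 88%, according to whether final values or changes were to be tested. Over ρ from 0.3 to 0.8 the first figure runs from 84% to above 99%, and the second from 94% down to 84%.

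These sizes rest on the assumed correlation and on equal SDs at baseline and follow-up. That ANCOVA has the lower variance holds, with equal SDs, for any correlation strictly between 0 and 1. The validity of the trial and its primary conclusion are not in question.

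**What to change.** In Methods of statistical analyses, replace the sentence on secondary endpoints. Each continuous secondary endpoint with a pre-randomization value is analyzed with the primary model: its own baseline as covariate, treatment as fixed effect, center as random effect. For skewed variables, name a log-scale or rank-based ANCOVA in advance.

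Exacerbation counts do not fit this model and stay outside the change. So does EOS, unless a baseline count is taken.

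The cost is wording only, with no new data, visits or patients. The article describes the trial as ongoing, so the change should be made and dated before unblinding.

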#### Safety evaluation

Adverse events are defined as unfavorable or unintended signs, symptoms or diseases occurring after the treatment that are not necessarily related to the acupuncture intervention. Any adverse event or abnormality will be recorded in the CRF regardless of relationship to the study intervention. If any serious adverse events occur, the intervention will be stopped immediately and appropriate action will be taken. This will be reported promptly to the institutional review board, according to the protocol.

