#### Exclusion criteria

Participants meeting any of the following criteria will be excluded:Participation in another clinical trial in the previous 1 month;Have received systemic corticosteroids in the previous 2 weeks;With systemic infection, respiratory infection, pulmonary tuberculosis and fungal infection in the previous 1 month;Hospitalization due to acute exacerbation of asthma in the previous 3 months or in the baseline period;Cannot stop using inhaled corticosteroids, theophylline, long-term β_2_ agonist, sodium cromoglicate, leukotriene antagonists, anticholinergic drugs or be allergic to albuterol and corticosteroids;Complicated with other severe primary diseases (including hypertension, cancer, hyperthyroidism, bronchiectasis, cardiac insufficiency) and conditions that would prevent participation in the trial or put the participant at risk;Women who are known to be pregnant or breastfeeding;Acupuncture contraindications, such as serious atopic or infectious dermatopathy and hemorrhagic diseases (including thrombocytopenic purpura and hemophilia).

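### The adverse-event definition starts at treatment, so events in the consented, no-treatment baseline week are not classed or reported as adverse events

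*Protocol article*

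**What the plan says.** All references are to the protocol article.

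- **Safety evaluation** defines adverse events as "unfavorable or unintended signs, symptoms or diseases occurring after the treatment that are not necessarily related to the acupuncture intervention". It then states: "Any adverse event or abnormality will be recorded in the CRF regardless of relationship to the study intervention". For serious adverse events it says: "This will be reported promptly to the institutional review board, according to the protocol".
- **Ethics and trial registration** requires written consent before any study procedure.
- **Procedure** says that, once the diagnosis is confirmed, "participants will enter a baseline period of 1 week without treatment". **Randomization** takes place after the baseline evaluation.
- **Exclusion criteria** rule out patients who "Cannot stop using inhaled corticosteroids, theophylline" or the other listed controller drugs. They also rule out "Hospitalization due to acute exacerbation of asthma in the previous 3 months or in the baseline period".
- **Interventions** asks patients to complete the case report form and to "record daily asthma symptom scores, acute asthma episodes and the use of as-needed salbutamol aerosol and/or prednisone tablets in the asthma diary", starting when screening is complete and ending with the last follow-up visit.
- **Methods of statistical analyses** limits the safety set to "All the randomized patients who receive at least one treatment and for whom any post-baseline safety data are available".

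**The concern.** A treatment-emergent window is a normal choice for analysis. Here, however, the start point is written into the definition of an adverse event itself, so everything that depends on the definition inherits it: what counts as serious, what goes to the review board, and what is summarized as safety data.

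The week left out is not a neutral one. Participants are already under trial consent, the trial itself makes the week treatment-free, and the eligibility rules require that controllers can be stopped. The authors expected that a serious exacerbation might occur then, because they list hospitalization in that period. What they attach to it is a screening consequence (the patient is excluded) and no stated safety consequence.

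At stake are oversight and complete reporting of harm. A hospitalization in a trial-required week could go unreported to the board as a serious adverse event, and the published safety results would describe only those who came through the baseline week and were treated.

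**Working it through.** The plan gives no figure on this point, so the check is a timeline with each rule laid against it.

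**Order of events**

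1. Written consent (Ethics and trial registration).
2. Screening and confirmation of diagnosis (Procedure).
3. Baseline, 1 week, without treatment (Procedure).
4. Randomization (Randomization).
5. Treatment, 20 sessions in 6 weeks (Interventions).
6. Follow-up, 3 months (Follow-up).

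**Which rules apply in which period**

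| Rule | Baseline week | Treatment and follow-up |
|---|---|---|
| Consent in force | yes | yes |
| Diary and case report form (Interventions) | yes | yes |
| Adverse-event definition (Safety evaluation) | no | yes |
| Serious-event report to the board (Safety evaluation) | no, because it depends on the definition | yes |
| Safety set (Methods of statistical analyses) | no: needs randomization, one treatment and post-baseline data | yes |

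The diary starts when screening is complete; the adverse-event definition starts at treatment. The mismatch is the baseline week. The right-hand column takes the treatment start as the first session. The wording could also mean after the whole course, which would widen the gap, so it needs repair in any case.

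**Tracing one case.** A consented patient is hospitalized for an exacerbation in the baseline week.

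- The exclusion criterion removes the patient before randomization.
- Without randomization or treatment, the patient is not in the safety set.
- The event did not occur after the treatment, so by definition it is not an adverse event and hence not a serious one.
- The board-reporting sentence, which concerns serious adverse events, is not triggered.
- The episode may be in the diary, and the hospitalization must be known for the exclusion to be applied. No safety output is described that would contain either.

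**Share of trial time.** Taking 3 months as about 13 weeks, a participant is observed for 1 + 6 + 13 = 20 weeks. The uncovered week is 1/20 = 5% of that.

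**Number of events.** This cannot be derived. The documents give no exacerbation rate for the week. Nor can the planned 200 participants (100 per group) serve as the denominator for hospitalizations: anyone hospitalized for exacerbation during baseline is excluded, so the randomized patients contribute none by construction. Such events would come from consented patients who were not randomized, and their number is not given.

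**The case against.** The strongest reply has four parts.

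**The data are collected.** The diary and case report form cover the baseline week and capture asthma episodes, symptoms and rescue use. The rule that any abnormality be entered in the case report form has no start date. This stands. A reader might infer that harm in that week goes unrecorded, and the documents do not support that. But a diary entry is not a serious-event report, and the board sentence concerns serious adverse events, not abnormalities.

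**The controllers may not have been stopped yet.** This also stands. The exclusion criterion gives no stop date, and a baseline without treatment could mean without acupuncture. That controllers are already off by then is a reasonable inference, not a stated fact. The gap in the adverse-event window exists either way.

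**The article defers to the full protocol.** The reporting sentence says so, and an article commonly leaves reporting procedure to that document. It therefore cannot be claimed that the board will in fact never hear of a baseline event. But deferral excuses silence; this article states a start point in the definition itself, and that start point is too late.

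**The arm comparison is unaffected, and most of the exposure is covered.** Both are correct. The baseline week precedes randomization, so no bias between arms follows. The treatment and follow-up periods lie inside the adverse-event window, and exacerbations are counted as a secondary outcome. A safety set of randomized, treated patients is conventional for comparing arms and should stay.

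**Conclusion.** The concern holds as a defect in classification and reporting. As written, an event in the consented, treatment-free baseline week is not an adverse event or a serious adverse event, does not trigger the stated board report, and has no place in the safety set, although the plan itself foresees hospitalization in that week.

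Its extent is one week per consented participant, about 5% of a participant's time in the trial. The number of events is unknown, and no count should be attached to it. One unreported hospitalization would be enough to matter for oversight.

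The conclusion rests on a literal reading of the definition and on treatment meaning the trial acupuncture. It does not depend on when controllers are stopped. The documents do not support reading it as a total failure to record harm, as a bias in the safety comparison, or as proof that the full protocol has the same gap. The change is worth making because it replaces a stated rule with a better one at little cost.

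**What to change.** Reconcile the Exclusion criteria, Procedure, Interventions, Methods of statistical analyses and Safety evaluation sections on one start date for safety data:

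- State that recording of adverse and serious adverse events, and prompt reporting of serious ones to the review board, begin at informed consent. Replace the ambiguous wording about the treatment with that start point.
- List baseline-week events separately, with counts, for all consented participants, including those not randomized. Use the diary and case report form data already being collected, and include hospitalizations found when the exclusion criterion is applied.
- Keep the randomized, treated safety set for the comparison between arms. Events that began before the first session go in the separate listing.
- State when controllers are stopped relative to the baseline week, so that the listing can be interpreted.

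The cost is a change of wording, slightly more recording during one week and one extra listing. Sample size, efficacy analysis and the between-arm safety comparison do not change.
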